### Intervention

The intervention is a psychotherapeutically guided, psychoeducational and group-based program designed to strengthen individual health and life skills. It was developed with the help of experienced psychological and medical psychotherapists and aims to improve the emotional, social, and problem-solving skills of each participant by synergistically combining a dynamic-interactional model with disorder-specific coping-oriented perspectives and integrating concepts, ideas, and experiences of existing self-management programs (e.g. the “Gesundheits- und Lebenskompetenz Training [GLK]”, the “HEDE [Health-Ease and Dis-Ease]-Training”, the “Bochumer Gesundheitstraining”, the “Hildesheimer Gesundheitstraining [HGT]”, or the “Zürcher Ressourcen Modell [ZRM]”) [26]. The intervention will be conducted in subgroups of 6–12 participants and led by psychotherapists trained explicitly for this purpose. The main phase consists of 12 2-h sessions over 6 months that address relevant health-associated topics and are conducted at biweekly intervals. Three additional 2-h sessions will take place at monthly intervals, in which the participants can jointly reflect on previous changes and consolidate a viable future perspective for improving their ability to cope with the disease. Each session will begin with an orientation round during which patients check in and prepare for the session. It will end with a closing round where patients can reflect on and share their experiences and insights from the session. This process helps to clarify possible misunderstandings and address any disappointments promptly.

Before the actual start of each 12 session intervention program, there will be a preliminary one-on-one meeting (approximately 45 min) with each participant conducted by the psychotherapist leading the group so they can familiarize with each other, clarify intervention expectations, and discuss possible intervention fears. Then, if necessary, there can be a second meeting.

The first phase of the intervention program (information phase) comprises six group sessions over 3 months at 2-week intervals, each lasting approximately 2 h. During the first two sessions, the objectives are to get to know each other, build mutual trust, and encourage confidence within the group. Furthermore, the program will be explained, and each patient will voice his or her personal health goals and expectations for the program. The subsequent four sessions (3–6) will address health-associated topics relevant to RA, e.g. nutrition, physical activity, sleep, and stress. Therefore, basic knowledge of each of the topics and its relevance to RA will be shared and subsequently deepened upon using a variety of group exercises, e.g. self-reflective or interactional. In this phase, patients will develop a biopsychosocial understanding of health and disease. This involves recognizing connections between psychological factors (e.g. stress, conflicts, persistent worries) and physical processes, and learning about possible ways to influence and personalize disease management.

The second phase of the intervention (open phase) will also last 3 months with six 2-h group sessions at 2-week intervals. During sessions 7–11, the psychotherapists will refrain from specifying the content of the discussion. Instead, participants will be actively encouraged to express their concerns, such as coping with stress or specific conflicts, and to receive support from the group. The aim of these sessions is to help patients identify personal resources and improve individual disease management, emotion regulation, and conviction of self-efficacy. In addition to the orientation and closing rounds, the structure of each session can vary depending on the topics introduced and discussed by participants and developing group dynamics. Finally, in the last session (12), the group will prepare for the end of the main phase of the program and reflect on progress and improvements.

The third phase of the intervention (sustainability phase) will also last 3 months but contains only three 2-h group sessions at monthly intervals. The psychotherapists will take a more active, leading role again and prepare the patients for detachment from the group and the transition to everyday life without the group. In the last session (15), the group members will reflect and give feedback on the program.

### Outcome measures

Measurements of the target variables and additional data will be collected at multiple time points throughout the study period by participating rheumatologists and psychotherapists (Fig. 1). The first measurement time will be a maximum of 2 weeks prior to the intervention as a baseline (*t*_0_). Then, five more measurements will be taken every 6 weeks during the 9 months of intervention (*t*_1_: 1.5 months after intervention start, *t*_2_: after 3 months, *t*_3_: after 4.5 months, *t*_4_: after 6 months, *t*_5_: after 9 months) and three more measurements will be taken every 3 months during the follow-up phase (*t*_6_: after 12 months, *t*_7_: after 15 months, *t*_8_: after 18 months). The time points will have a temporal range of ± 2 weeks for each proband, depending on each participant’s appointment at the rheumatologist’s office.

The psychological condition of each participant will be determined with a set of questionnaires. The State-Trait Anger Expression Inventory-2 (STAXI-2) is a questionnaire that measures various aspects of anger as an emotional state (state anger) and the disposition to experience angry feelings as a personality trait (trait anger) [27]. The Toronto Alexithymia Scale (TAS-26) assesses difficulties in identifying and describing feelings or emotions [28]. The 12-item Short Form Survey (SF-12) captures the general physical and mental health status and its implications for an individual’s everyday life [29].

The Health Education Impact Questionnaire (heiQ) measures the effectiveness of the group intervention related to the proximal outcome criteria of compliance, self-efficacy, and health behaviours, collectively understood as health literacy [30]. The Pittsburgh Sleep Quality Index (PSQI) assesses sleep quality, sleep disturbance, and possible sleep disorders [31]. The Depression Module of the Patient Health Questionnaire (PHQ-9) measures the severity of depression by scoring all nine DSM-IV depression criteria [32]. Last, the PETRA questionnaire was developed to be complementary to the other questionnaires to assess possible influencing factors on the course of the disease, i.e. current psychotherapeutic treatment, life events, physical activity and relaxation exercises. These questionnaires will be administered at all time points (*t*_0_–*t*_8_) during the rheumatologist appointments, except for the PSQI, which will be distributed only every 3 months (*t*_0_, *t*_2_, *t*_4_, and *t*_6_–*t*_8_). At the beginning of the intervention, patients in the intervention group will also complete the NEO Five-Factor Inventory (NEO-FFI), which evaluates the five domains of personality: neuroticism, extraversion, openness, agreeableness, and conscientiousness [33].

Physiological measurements will be assessed in blood and saliva samples, which the rheumatologists will collect at each appointment from the patients. Several cytokines and associated parameters, namely, tumour necrosis factor α (TNF-α), interleukin-1β (IL-1β), interleukin-2 (IL-2), interleukin-2 receptor (IL-2R), interleukin-6 (IL-6), interleukin-10 (IL-10), interleukin-12 (IL-12), interleukin-13 (IL-13), C-reactive protein (CRP), and erythrocyte sedimentation rate (ESR), will be analysed in plasma samples to assess immune system activity. Furthermore, cortisol levels will be measured in saliva samples. Cytokine and cortisol concentrations will be assessed at all time points. Additionally, at *t*_0_, anti-citrullinated protein antibody (ACPA) and IgG Fc autoantibody (rheumatic factor) levels will be measured. The rheumatologists are responsible for sampling and preprocessing all specimens and will determine ACPA, rheumatic factor, and CRP/ESR levels at *t*_0_, *t*_1_, *t*_3_, and *t*_5_–*t*_8_ within the frame of standard patient care. An external professional laboratory will be engaged to perform all other biochemical analyses in this study. For shipment from the rheumatologists to the laboratory, blood samples will be centrifuged (3000 rpm for 10 min) in serum gel tubes and subsequently stored at − 20 °C, and saliva samples will be collected using a cotton swab and shipped at room temperature.

RA disease activity will be measured using the Disease Activity Score 28 (DAS 28), the Simplified Disease Activity Index (SDAI), and the Clinical Disease Activity Index (CDAI) [34]. These composite scores are standard in clinical practice and based on questions about rheumatic pain, swelling, and tenderness of joints evaluated by the patient and the attending physician, combined with levels of CRP/ESR. Additionally, the Hannover Functional Ability Questionnaire (FFbH) will be conducted to assess functional capacity and impairment during rheumatic patients’ daily activities [35]; the patients rate their overall pain on a 10 cm visual analogue scale (VAS). The DAS 28, SDAI, CDAI, and pain VAS will be assessed at all measurement time points by the rheumatologists; the FFbH will be administered at every second time point (*t*_0_, *t*_2_, *t*_4_, *t*_6_, and *t*_8_).

Healthcare-related costs for each patient will be assessed using routine health insurance data. For this purpose, the number and type of all physician visits, supplementary therapies, drug costs, the number and duration of hospital stays, days of incapacity to work and the resulting inpatient, outpatient, and total health insurance expenditures over the 18-month study period (from *t*_0_ to *t*_8_) will be obtained from the respective healthcare provider.

Patients from the intervention group and each psychotherapist leading a group will evaluate their perception and experience of the training and provide this information via newly developed questionnaires at the beginning and end of the intervention program.

Additionally, BMI, concomitant diseases, and rheumatic medication intake will be assessed as control variables. Height, weight, and concomitant diseases will be captured at *t*_0_ and *t*_8_, and the rheumatologists will provide the medication regimen at each time point. The following types of medication will be considered: cortisone preparations, conventional synthetic or targeted synthetic disease-modifying antirheumatic drugs (cs/tsDMARD), and biological or biosimilar disease-modifying antirheumatic drugs (b/bsDMARD).

### Integrative single-case studies

A subset of ten patients (five from the intervention group and five from the control group) will be monitored closely before and after the intervention phase in the form of integrative single-case studies performed by the MUI [23]. Shortly before the start of each of these studies, a patient will undergo a thorough physical exam by his or her rheumatologist. Moreover, interviews (e.g. Structured Clinical Interview for DSM-5 [SCID-5], Life Events and Difficulties Schedule [LEDS], Operationalized Psychodynamic Diagnosis [OPD]) will be conducted in person with patients for the following purposes: (1) psychiatric evaluation, (2) recording the previous 2 years’ life events and difficulties, (3) obtaining in-depth information about the patient’s biopsychosocial biography, and (4) getting to know patients and establishing a trusting relationship for the upcoming weekly interviews.

During the data sampling period of the integrative single-case studies, patients will collect all of their urine in 12-h intervals (~8 am to ~8 pm and ~8 pm to ~8 am) for a period of approximately 1 month. Upon collection, Na-metabisulfite and Na-EDTA will be added to the urine canisters to prevent sedimentation and oxidation. After collection and aliquotation, samples will be stored at − 20 °C at home for the study duration and afterwards at − 80 °C in the clinic until further analysis of various stress system and immune parameters such as urinary cortisol, neopterin, and IL-6.

Furthermore, patients will retrospectively complete a set of questionnaires at the end of each 12-h interval, i.e. at ~8 am and ~8 pm. Specifically, using an adapted version of the Daily Inventory of Activity, Routine and Illness (DIARI), the patient will answer questions about RA symptoms, daily lifestyle factors (e.g. physical activity, alcohol consumption, medication, sleep behaviour), psychological factors (e.g. emotional states, emotional competence, social support), and potential signs of infection. Moreover, the patient will take notes on all psychosocial incidents (positive and negative) during the preceding 12 h.

Furthermore, weekly in-depth psychological interviews (lasting approximately 1 h) using the Incidents and Hassles Inventory (IHI) will be conducted with the patient via online videoconferences. These interviews aim to identify the previous week's negative and positive emotionally meaningful incidents, which will subsequently be rated by a three-person panel following the study period. Additionally, the patients will have weekly appointments with their rheumatologists to determine their DAS 28 (CRP/ESR), SDAI, and CDAI scores.

Using the integrative single-case design, researchers can construct various equidistant time series from biological, psychological, and social datasets. These time series can be statistically analysed to determine their temporal relationships. For instance, one can investigate whether one variable significantly precedes or follows another [36, 37], identify response patterns between variables [17, 38], and determine the duration of temporal delays between variables [39, 40]. For further details on the study design, see [23].

Before the intervention begins, all ten patients participating in the integrative single-case studies will collect data as previously described for the 3-month period leading up to the intervention. In contrast, the follow-up data collection periods are staggered: two patients will be monitored within 1 to 4 months after the intervention ends, four patients within 5 to 8 months after, and four more patients within 9 to 12 months after, each for approximately 1 month. This design allows for the identification of functional changes before and after the intervention, such as alterations in the patients’ psychophysiological response to emotionally meaningful positive and negative incidents.

### Study procedures and data management

Patients who want to participate in the study will receive informational materials from their respective (participating) rheumatologist, which contains a comprehensive and understandable study description. The consent form (for the study in general and the integrative single-case studies specifically) will also be provided by the rheumatologist, who will pass it on either to BKK-LV Bayern or AOK Bayern (dependent on the patient’s insurance) after the patient signed it. Patients must provide written, informed consent before any study procedures can occur. Participating patients will indicate their consent by signing a form in which they agree to the use of their data for the specific purposes. Only data pertinent to project implementation and scientific monitoring will be gathered, processed, and utilized. Patients have the right to withdraw their consent at any time without needing to provide reasons.

The data protection concept follows the principle that at no time will clear names and patient data be present in a dataset. For this purpose, all patients will be given pseudonyms on the basis of a randomization list that has been created by the UR. Collection, merging, evaluation, and storage of the data in paper form will be carried out by different institutions. Participating patients will be randomly assigned into an intervention group or a control group. The BKK-LV Bayern and the AOK Bayern will randomize the enrolled patients to the intervention or control group based on previously created pseudonymized participant IDs. Within the project consortium, conclusions about the person will be possible only for the BKK-LV Bayern and the AOK Bayern, as well as for the patient controller with the help of the key table. The blank randomization lists will be password-protected, encrypted and stored in a secure FTPS directory.

After enrolment, the patients will be randomly allocated to the intervention or control group in a 1:1 ratio, alternately dependent on the time of registration, using a prefabricated list of pseudonymous six-digit proband IDs created using the *random*-package in Python [41]. These IDs will be used to combine data from different sources for evaluation purposes pseudonymously. The UR will be responsible for evaluating study data and monitoring the project progress, whereby data from different sources (RheMIT, archive service provider, laboratory, BKK-LV Bayern, AOK Bayern) will be combined and sorted according to the proband IDs. If missing data or unattended appointments are found, the UR will contact respective responsibilities to evaluate further procedures.

A designated proband guide will handle a large part of the communication and information flow towards patients, rheumatologists, and psychotherapists. The BKK-LV Bayern and AOK Bayern will inform the proband guide about each enrolled patient, who will then inform the patients about their group allocation and patients in the intervention group about possible intervention subgroups near them. When 6–12 participants are available for a subgroup, the proband guide will close admissions for that subgroup, set an intervention start date, and provide the participants' contact information and questionnaire copies (NEO-FFI, anamnesis and evaluation form) to the assigned psychotherapist. Each psychotherapist leading a subgroup will track the attendance of participants at each session and transmit lists to an archive service provider, who will forward these to the UR.

Furthermore, the proband guide will inform the rheumatologists of the patients in each subgroup so that they can arrange appointments at the measurement time points (*t*_0_–*t*_8_). For secure exports of datasets to the study's evaluators, some of the measurements that are assessed in these appointments (CRP/ESR, SDAI, CDAI, DAS 28, VAS, PHQ9, FFbH, PSQI, BMI, medication, comorbidities, rheumatic factor levels, ACPA levels) will be documented by the rheumatologists using standardized forms in particular software (RheMIT | BDRh Service GmbH [bdrh-service.de]). The UR will receive the pseudonymized (proband ID) data for all patients, while the MUI will receive only data for the integrative single-case study patients. Other questionnaires, which will also be administered at the appointments and cannot be documented in RheMIT (STAXI-2, TAS-26, SF-12, heiQ, PETRA-Questionnaire), and the questionnaires, which will be completed during the intervention’s group sessions with the psychotherapist, will be mailed by the rheumatologists and psychotherapists to an archive service provider, who will digitalize the data and forward it to the UR. Data from the integrative single-case study participants will then be sent to the MUI by the UR. The data on healthcare-related costs will be pseudonymized and sent directly to the UR by BKK-LV Bayern and AOK Bayern.

For physiological measurements performed by the external professional laboratory, the rheumatologists will send preprocessed samples (blood and saliva) to the laboratory, where the mentioned biochemical analyses will be performed, and the pseudonymized results will be transmitted to the UR. In the integrative single-case studies, laboratory equipment necessary for urine sampling and storage and all questionnaires will be provided to the patients before the data sampling period starts and will be picked up afterwards by the MUI. The MUI will perform subsequent biochemical analyses of urine samples.

All patient data transfers will be performed securely, either by mail or encrypted email. The data flow architecture and study procedures have been reviewed and approved by the Bavarian state commissioner for data protection. In this study, a data monitoring committee has not been established. To ensure that the data from the various sources are transferred securely to the UR (evaluating institution), a server will be rented from the company Pegasus GmbH. Pegasus GmbH will assume the role of security management and manage server hosting. Pegasus GmbH is ISO/IEC 27001 and ISO/IEC 27018 certified. The servers are in Germany. Before the exchange, all files to be transmitted will be encrypted. For this purpose, asynchronous encryption is used. Each partner, similar to the UR, creates a private and a public key, and they exchange these keys among one another. The files are signed using the partner’s private key so that the recipient can verify the sender’s source, and the files are encrypted using the partner’s public key so that only the owner of the key counterpart can decrypt them. The study design is open-label with only outcome assessors being blinded, so unblinding will not occur.

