### Population, recruitment, and allocation

The study population will consist of patients diagnosed with seropositive chronic polyarthritis (ICD-10-Code M05) or another chronic polyarthritis (ICD-10-Code M06) with a minimum age of 18, who are being treated by an eligible rheumatologist in Bavaria and are insured with either BKK-LV Bayern or AOK Bayern. Furthermore, participants need to have sufficient German language skills to complete the questionnaires used by the study. Patients with a diagnosis of fibromyalgia (ICD-10-Code M79.7) will be excluded from the study. The probands will primarily be recruited with the assistance of rheumatologists who practice in the study region and will introduce the study to their patients. Furthermore, the study will be promoted in relevant self-help networks, and some patients who gave prior consent to receive such offers will get a postal notification by BKK-LV Bayern or AOK Bayern. The goal is to enrol 440 probands, who will be randomized in equal proportions into the intervention and control groups (each *n* = 220). Based on simulations using the *lme4* package in *R* [24, 25], this sample should allow the identification of even small effects (*f* = 0.1) with adequate statistical power (1 – *β* > 0.8) while considering a possible drop-out rate of 20%.

Prior to patient enrolment, eligible registered rheumatologists in Bavaria will be contacted and asked to participate in the study. After application and confirmation of participation, the rheumatologists will receive comprehensive instructions on their tasks and responsibilities within the study. In addition, psychotherapists can apply to lead an intervention subgroup. Before the study starts, psychotherapists will be selected from the applicants using an assessment process and receive comprehensive training in the content, background, and implementation of the PETRA intervention program (“train the trainer”).

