## Trial status

(Protocol version 5.0, 24th October 2023)

Recruiting started on 1st February 2022 and ended on 30th September 2023. The study successfully enrolled a total of 73 individuals, with 34 participants in the control group (2 withdrawals) and 39 participants in the intervention group (8 withdrawals). As of now, one integrative single-case study has been conducted. Additional integrative single-case studies are pursued.

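### The allocation sentence calls assignment random but describes alternation by registration time, and the reported 34:39 does not fit that rule on one list or on one list per insurer

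*Protocol article*

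**What the plan says.** The abstract of the Protocol article calls the study a randomised controlled trial. The section on population, recruitment and allocation plans 440 patients "who will be randomized in equal proportions into the intervention and control groups", 220 in each.

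The mechanism is given in Study procedures and data management:

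- The two insurers "will randomize the enrolled patients to the intervention or control group based on previously created pseudonymized participant IDs".
- Patients are "randomly allocated to the intervention or control group in a 1:1 ratio, alternately dependent on the time of registration". The sentence continues "using a prefabricated list of pseudonymous six-digit proband IDs created using the" *random* package in Python. That clause concerns the IDs. No random sequence of arms, block or stratum is described.
- On protection of the sequence: "The blank randomization lists will be password-protected, encrypted and stored in a secure FTPS directory". Lists are in the plural, and their number is not given.
- The rheumatologist passes the signed consent form to the insurer. Within the consortium, only the insurers and a patient controller can link the pseudonym to the person.
- A patient guide is told of each enrolled patient and informs patients of their arm.

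The same section says the design is open-label, with only outcome assessors blinded. On the result, Trial status gives 73 as the number enrolled and splits this by arm: "34 participants in the control group (2 withdrawals) and 39 participants in the intervention group (8 withdrawals").

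**The concern.** One sentence makes two incompatible statements. Random allocation means that the next arm cannot be known from the previous ones. Alternation by order of registration means that it can. Attaching a randomly generated six-digit number to each patient does not change this: the ID is random, but the arm sequence is not.

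Under alternation, a person who knows the last assignment predicts the next with probability 1, against 0.5 under simple randomisation. The insurers are in that position, because they handle incoming consent forms, can identify patients and assign the arm. They also send study invitations to some patients. The patient guide learns the assignments as they are made.

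Every between-group comparison in the Statistical analyses section rests on the allocation. If arms were alternated, the protection against selection between arms is weaker than the design label promises. Adjusting for covariates does not restore it. The reported arm sizes add a second question, because they do not look like the output of an alternating rule.

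**Working it through.** **Inputs (Protocol article).** Total enrolled 73, control 34 with 2 withdrawals, intervention 39 with 8 withdrawals (Trial status). Ratio 1:1 with alternation by registration time; two insurers allocate; lists in the plural, number not stated (Study procedures and data management).

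**Step 1: what the counts include.**

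- As printed: 34 + 39 = 73, the stated total. Difference 39 − 34 = 5.
- Withdrawals added on top: 36 + 47 = 83, which is not 73. This reading is ruled out.
- Withdrawals removed: 32 + 31 = 63, which is not 73 either.

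The withdrawals are therefore inside the 34 and 39, and the difference to explain is 5.

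**Step 2: what alternation can produce.** A strictly alternating list of any length has arms that differ by 0 (even count) or 1 (odd count). With k separate lists the total difference is at most k. It must also have the same parity as the total, and 73 is odd.

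| Alternating lists | Possible differences with 73 patients | Is 5 possible? |
|---|---|---|
| 1 or 2 | 1 | no |
| 3 or 4 | 1, 3 | no |
| 5 or 6 | 1, 3, 5 | yes |

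One list gives 36:37 or 37:36. One list per insurer (two lists) also gives a difference of exactly 1. A difference of 5 needs at least five lists. With exactly five, all must end on an odd count with the same arm ahead. If each starting arm were chosen at random, five odd-length lists would all lean the same way with probability 2 × (1/2)^5 = 0.0625. If all lists started with the same arm, it would happen whenever all five ended odd.

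**Step 3: what other mechanisms would produce.**

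- Simple 1:1 randomisation: with X the number in the intervention arm, X ~ Binomial(73, 0.5), P(difference ≥ 5) = 2 × P(X ≥ 39) = 0.64.
- Permuted blocks on a single list: the largest imbalance is half the block size, so 5 needs a block of at least 10.

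**Step 4: text and counts side by side.** The text, read literally, describes a deterministic rule. The counts fit that rule only under conditions the article does not mention, and they fit simple randomisation easily. The stated rule and the reported result disagree.

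**The case against.** The strongest reply is that the sentence is clumsy and the trial sound. The same section mentions a randomisation list made by the evaluating university and a list prepared in advance with a random generator. The phrase about alternation may only mean that the next list entry is taken in order of registration. The full protocol exists and might say so. This reading is possible, and the 0.64 is compatible with it. It does not rescue the sentence: the article credits the generator with the IDs alone and says outright that allocation alternates. This is a mechanism stated, not a detail left out.

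Second, predictability is limited. Allocation follows enrolment and consent, recruiting rheumatologists do not assign arms, and the lists are encrypted. Nothing says that recruiters see the running sequence or that insurers know who is receptive to psychological treatment. This stands, and it limits the likely harm. It does not remove the insurers' own position.

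Third, a reader might infer that 34:39 cannot have come from alternation. The documents do not support that. The number of lists is not given, and one insurer body is an association of company funds, so more than two lists are conceivable. After withdrawals the arms stand at 32:31, so replacement of withdrawn patients or omission of some allocated patients could also play a part. The article describes none of this.

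Fourth, a reader might take the Discussion's remark on receptive patients as an admission of steering between arms. It is not: it concerns who volunteers for the trial, before allocation and for both arms.

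**Conclusion.** The allocation description is wrong as written. It contradicts itself and, taken literally, describes alternation, which would make this a quasi-randomised trial. The reported difference of 5 does not match alternation on one list or on one list per insurer, where it would be exactly 1.

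This rests on two assumptions: that 34 and 39 include the withdrawals, which their sum of 73 supports, and that no more than four alternating lists were in use, which the article neither states nor excludes.

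A reader might go further and conclude that the allocation was not random, or that the arms are biased. The documents do not support that. The two observations pull in different directions: if the counts speak against alternation, they also speak against predictable assignment as actually carried out, and a split at least this uneven has probability 0.64 under simple randomisation. No manipulation is shown, and no size of bias can be derived from the documents. What is established is a mismatch on the feature that justifies every between-group conclusion. Whether the mechanism was misdescribed or not followed, the text needs correction.

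**What to change.** Check the existing allocation list, or lists, against the registration dates. Then state in the protocol and in every report:

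1. how the sequence of arms, as distinct from the IDs, was generated;
2. how many lists were used and who held each;
3. who could see the next assignment before it was made;
4. how 34:39 arose, including whether withdrawals affected later assignments and whether any allocated patient is missing from the 73.

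Then take one of two routes:

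- **If arms were alternated:** call the trial quasi-randomised in the protocol and reports, analyse patients as allocated, and add insurer and registration date as covariates in the mixed models. Both should already be on record.
- **If a random list was used:** delete the clause about alternation by registration time and describe the list.

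Recruitment ended on 30 September 2023, so the remedy is verification and honest labelling, not a new allocation scheme. The cost is an audit of a list that already exists, a few sentences and at most two covariates. The real downside is that the audit may confirm alternation, and the trial would then carry a weaker design label.
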